## STUDY SUMMARY IN LOCAL LANGUAGE

Apnoe-Oxygenierung geht in der Geschichte der Anästhesiologie weit zurück. Dies hat deshalb einen grossen Wert, weil es bei jeder Allgemeinanästhesie zu einer kurzen Phase der Apnoe kommt, bevor der tracheale Tubus platziert werden kann. Dieses Prozedere ist sehr sicher. Sehr selten kann es aber zu unerwarteten Schwierigkeiten kommen, die innerhalb weniger Minuten zu einer Entsättigung des Patienten führen. Möglichkeiten diese Zeit zu verlängern sind deshalb von Patientensicherheitsseite wünschenswert.

In den letzten Jahren ist insbesondere die Anwendung von HFNCT (high flow nasal cannula therapy, Therapie via Nasensonde mit hohen Flussraten) im Bereich der trachealen und

laryngealen Chirurgie in den Vordergrund getreten. Hierfür wird Sauerstoff erwärmt und angefeuchtet, damit er unter Flussraten von bis zu 70 l/min über die Nase insuffliert werden kann. Unter dem Namen THRIVE (transnasal humidified rapid-insufflation ventilatory exchange) wurde dieses Verfahren bei Patienten mit kontinuierlicher Laryngoskopie etabliert. Dieser Name ist durch lange Apnoezeiten (bis 65 Minuten), und durch den beobachteten, langsamer als erwarteten CO2 Anstieg gekennzeichnet. Es wird angenommen, dass durch die hohen Flussraten Turbulenzen entstehen, die sich über die Trachea bis in die Alveolen fortsetzen und somit zu einer gewissen CO2-Auswaschung führen, was aber bisher nicht bewiesen werden konnte.

Eine kürzlich durch unsere Studiengruppe durchgeführte Studie von Riva et al. (British Journal of Anaesthesia, 2018, in press) an Kindern widerlegte allerdings diesen Ventilations-Effekt bei Kindern. Die Datenlage bei Erwachsenen ist noch lückenhaft, insbesondere bei unterschiedlichen Flussraten und deshalb wollen wir hier eine genauere Untersuchung starten.

Dafür sollen insgesamt 100 Patienten rekrutiert werden, die im Rahmen eines elektiven chirurgischen Eingriffs eine Allgemeinanästhesie erhalten müssen. Unsere Untersuchung wird dafür in den normalen Ablauf der Anästhesie-Einleitung eingebettet.

Bevor die Anästhesie eingeleitet werden kann, muss der Patient präoxygeniert werden. Anschliessend wird die Narkose eingeleitet. Wenn der Patient bewusstlos ist, wird mit Maskenatmung begonnen und die randomisierte Zuteilung in die unterschiedlichen Interventionsgruppen aufgedeckt.

Eine der folgenden vier Massnahmen wird anschliessend durchgeführt: THRIVE mit 70 l/min unter Anwendung des Esmarch Manövers (jaw thrust), THRIVE mit 70 l/min unter permanenter Laryngoskopie (Kontroll-Gruppe), 10 l/min mit Esmarch oder 2 l/min mit Esmarch.

Währenddessen werden EKG, Pulsoxymetrie, Narcotrend™, transkutanes pCO2 und pO2, NIRS, Elektrische-Impedanz-Tomographie, Blutdruck und Herzzeitvolumen (mit FloTrac über Pulsdruckkurven) kontinuierlich aufgezeichnet. Ausserdem werden alle zwei Minuten arterielle Blutgasanalysen durchgeführt.

Die zugeteilte Massnahme erfolgt bis entweder SaO2 < 92%, PtcCO2 > 80 mmHg oder Zeit > 15 Minuten aufgetreten sind. Sollte der pH < 7.10 fallen oder das Kalium > 6.0 mmol/l steigen, wird das Experiment ebenfalls abgebrochen.

Anschliessend wird der Atemweg gesichert und normal mit der Anästhesie fortgefahren.

Bevor der Patient entlassen wird, führen wir eine Befragung durch, wo allfällige Nebenwirkungen und Komplikationen des Atemwegmanagements erfragt werden.

Unsere Hauptfrage ist, wie unterschiedliche Flussraten und Mundöffnung die CO2 Auswaschung beeinflussen, wobei wir davon ausgehen, dass die tieferen Flussraten nicht relevant schlechter sind. Zusätzlich werden wir mit NIRS nicht invasiver Messung über der Haut der Stirn den Effekt des erhöhten CO2 auf die zerebrale Durchblutung messen, mittels EIT bestimmen wir Änderungen der funktionellen Residualkapazität der Lungen und wir können über Veränderungen Aussagen über potentiell auftretende Atelektasen treffen. Ausserdem können auch arterielle Messungen von pO2 und pCO2 mit den transkutanen Messungen verglichen werden.

Durch die Erkenntnisse dieser Studie erwarten wir, in Zukunft die apnoeische Oxgenation auch mit niedrigeren Flussraten durchführen zu können, was nicht nur weniger O2 verbraucht, sondern auch materialtechnisch gesehen deutlich billiger ist. Auch ist die

Verfügbarkeit von normalen Nasenbrillen in jedem Operationssaal und sogar auf Abteilungen überall gegeben, wohingegen THRIVE-basierte Systeme deutlich seltener vorhanden sind. Insbesondere bei einem Atemwegsnotfall wäre eine schnell verfügbare Alternative wichtig, um eine schnelle Desaturierung bei prolongierter Atemwegsicherung zu vermeiden. Schliesslich gibt es keine Evidenz, welche physiologische Veränderungen bei anästhesierten Patienten stattfinden, die nun routinemässig bis zu einer Stunde ohne Ventilation oxygeniert werden.

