
|                      |                                                                                                                                                                                                                                                                                                                                                                                                                                                                                                                                                                                                                                                                                                                                                                                                                                  |
|----------------------|----------------------------------------------------------------------------------------------------------------------------------------------------------------------------------------------------------------------------------------------------------------------------------------------------------------------------------------------------------------------------------------------------------------------------------------------------------------------------------------------------------------------------------------------------------------------------------------------------------------------------------------------------------------------------------------------------------------------------------------------------------------------------------------------------------------------------------|
| Objective(s): | 
This study compares under controlled conditions if different flow rates affect apnoea time after induction of anaesthesia and how CO2 clearance is influenced. Furthermore, this study enables to quantify the effects of increased pCO2 on cerebral perfusion.
 
Our primary hypothesis states that any of the three intervention is non-inferior to HFNCT regarding clearance of CO2 (ventilatory effect).
                                                                                                                                                                                                                                                                                                                                                                        |

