### **2.1 Ethical considerations**

#### **2.1.1 The potential gain of new knowledge obtained with this study, and its meaning for patients/society:**

With this study, we will be able to determine, if high flow nasal cannula therapy (HFNCT) provides a real benefit over medium flow or low nasal cannula therapy. This can be of use in emergency situations, where airway access is sometimes difficult to obtain as apnoeic oxygenation could prolong apnoea time until desaturation. Lower flow rates can be provided in almost all clinical settings, including preclinical situations and on medical wards through already available systems. For HFNCT, a specific device is necessary, the availability of which is very limited. If non-inferiority can be shown, it could result in a greater safety for all patients through widespread availability of oxygen therapy devices, at a reduced cost compared to HFNCT. Furthermore, there is no evidence available about the physiological

changes in anaesthetised patients undergoing HFNCT for a prolonged time, which now has been established as a standard procedure.

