### **2.1.2 Assessment of the benefit/risk relationship for the patient.**

HFNCT and apnoeic oxygenation are concepts that have been provided with enough evidence to sustain their acceptance in clinical use. There have even been studies suggesting possibility of oxygenation, using very low flows of oxygen [7-9]. But both, high flow and low flow have never been directly compared for its influence on human physiology. However small the risk, desaturation in low-flow groups cannot be completely ruled out. But one of our endpoints is saturation of <92% after which the experiment will be discontinued. Saturation of 92% does not lead to any ischemic damage in healthy patients and all patients with known risks or vulnerability of ischemic events are excluded.

Furthermore,  $p_a\text{CO}_2$  will rise, this leads to a cerebral vasodilation. There is no data setting any threshold after which potential damage would occur, even though patients with  $p_a\text{CO}_2$  up to 250 mmHg have been shown to recover without any neurological impairment [4]. Our limit will be set at 80 mmHg, which therefore should not lead to any neurological damage whatsoever, especially since all patients with high vulnerability towards hypercapnia are excluded. Measuring near infrared spectroscopy (NIRS) will furthermore ensure, that cerebral perfusion will stay within normal limits.

$\text{CO}_2$  is known to have haemodynamic influence [10, 11], but our pilot data suggest that anaesthetic drugs like Propofol and Remifentanyl overrule this effect, as median blood pressure never exceeded 80mmHg.

Patients safety will not be compromised during the study time, as this procedure has shown to prevent desaturation up to 65 minutes [2, 12]. If unexpected difficult airway should occur in these patients, there is more time for securing the airway until desaturation will set in.

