### **3.4 Dose Rationale: Rationale for the intended purpose in study**

High Flow (70 l/min): THRIVE is normally used with very high flows, this is standard procedure

Medium Flow (10 l/min): Every anaesthetic respirator or oxygen wall connection can provide

10 l/min, which in emergency situation would be superior due to its higher availability.

Low Flow (2 l/min): Low flows could even be used with dry oxygen. This would reduce cost even further, and could find application in prevention of desaturation in high risk situations.

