## 8.5 Assessments of outcomes

### 8.5.1 Assessment of primary outcome

Transcutaneous CO2 will be measured throughout the study period by TCM4, Radiometer™, Thalwil, Switzerland; by applying a probe over the patient's chest. This is a standard procedure used very often during anaesthesia without complications.

Increase in ptcCO2 in mmHg/min will be calculated by dividing the difference of ptcCO2 by the time of the measurement, once linear increase has set in. In our pilot study, we have found transcutaneous ptcCO2 to have a little delay (about 60-90 seconds) after which linear rise sets in.

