## 10. STATISTICAL METHODS

### 10.1 Hypothesis

Null hypothesis: The difference of the mean increase of  $p_{tc}CO_2$  between any of the three intervention groups and the control group is at least 0.3 mmHg/min, the control group being lower.

Primary hypothesis: the difference of the mean increase of  $p_{tc}CO_2$  between the groups is less than 0.3 mmHg/min (non-inferior margin), one-sided testing. This hypothesis was based on a small clinical pilot study that showed no differences regardless of flowrate or mouth opening (jaw-thrust vs. laryngoscopy).

Secondary outcome hypothesis: The number of patients not tolerating the apnoea time of 15 minutes is not significantly higher in any of the three intervention groups.

Secondary outcome hypothesis: no significant changes in vital parameters such as cerebral perfusion will be recorded.

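### Section 2.1.1 ties a patient-safety benefit to non-inferiority, but non-inferiority is tested only on the CO2 slope, and the secondary hypothesis on apnoea tolerance does not supply the missing evidence on oxygenation

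*Protocol*

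**What the plan says.** **What is tested.** The synopsis states the primary hypothesis as "any of the three intervention is non-inferior to HFNCT regarding clearance of" CO2. Section 10.1 puts it as a difference in mean ptcCO2 increase that "between the groups is less than 0.3 mmHg/min (non-inferior margin), one-sided testing". Section 8.5.1 computes the endpoint as the change in ptcCO2 divided "by the time of the measurement, once linear increase has set in". Section 10.2 justifies the margin by CO2 alone: 9 mmHg over 30 minutes, set against a normal arterial range of 11 mmHg.

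**What is said to follow.** Section 2.1.1 opens with emergencies in which apnoeic oxygenation might lengthen the time to desaturation. It then makes a safety benefit conditional on the verdict: "If non-inferiority can be shown, it could result in a greater safety for all patients through widespread availability of oxygen therapy devices". Two other places speak about oxygenation without mentioning non-inferiority. The local-language summary expects "Durch die Erkenntnisse dieser Studie erwarten wir, in Zukunft die apnoeische Oxgenation auch mit niedrigeren Flussraten durchführen zu können" and says a quickly available alternative would matter in an airway emergency, "um eine schnelle Desaturierung bei prolongierter Atemwegsicherung zu vermeiden". Section 3.4 says of low flow that it "could find application in prevention of desaturation in high risk situations".

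**How desaturation is handled.** Under 6.1 a run ends at SpO2 <92%, ptcCO2 >80 mmHg, pH <7.1, potassium >6.0 mmol/l or more than 15 minutes. Time to 92% and lowest saturation are secondary outcomes (5.2). Section 10.1 adds a secondary hypothesis that no intervention arm has significantly more patients who fail to tolerate 15 minutes of apnoea. Section 2.1.2 concedes that "desaturation in low-flow groups cannot be completely ruled out".

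**The concern.** In 2.1.1 the condition is non-inferiority and the benefit is safety when the airway is hard to secure, where time to desaturation is what counts. A verdict on CO2 clearance does not show that a lower flow oxygenates as well. A reader who takes 2.1.1 at face value could turn a CO2 result into support for lower flows in emergencies, and the error would run towards too much reassurance.

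The secondary hypothesis in 10.1 is the nearest thing to a check on oxygenation. It expects the absence of a significant excess. With 25 per arm that absence is easy to obtain, and the count does not separate desaturation from the other reasons for stopping.

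**Working it through.** **1. The plan's own figure.** Inputs from 10.2: margin 0.3, SD 0.35, one-sided alpha 0.025, power 80%, true difference 0.

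n = 2 × (1.960 + 0.842)² × 0.35² / 0.3² = 21.4, so 22 per group. This agrees with the protocol. At 25 per group the power is 84.4% (t-based). The sample size is sound for the CO2 question.

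**2. What an early stop does to the endpoint.** Take 1.8 mmHg/min (10.2) and a linear phase starting at 1.5 minutes (upper end of the 60–90 s delay in 8.5.1).

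- Run completed: 13.5 min × 1.8 = 24.3 mmHg; 24.3 / 13.5 = 1.8.
- Run stopped at 6 minutes for SpO2 <92% (time assumed): 4.5 min × 1.8 = 8.1 mmHg; 8.1 / 4.5 = 1.8.

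The two contribute the same value in expectation. A shorter window only makes the slope noisier. In a simulation with equal true slopes and 25 per arm, non-inferiority was declared in 84.4% of runs whether 0%, 20% or 40% of one arm stopped early. With an assumed reading error of SD 1 mmHg and stops at 3–10 minutes the figures were 81.0%, 79.5% and 77.9%. Equal slopes are a premise here, so this illustrates the definition in 8.5.1. It is not evidence about how the arms will behave.

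**3. What the secondary hypothesis would accept.** Suppose 0/25 control patients and 5/25 in one intervention arm fail to reach 15 minutes.

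Two-sided Fisher p = 2 × C(25,5) / C(50,5) = 2 × 53,130 / 2,118,760 = 0.0502.

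At the two-sided 5% level (assumed; 10.1 gives none for this hypothesis) a 20-point excess is not significant, so the hypothesis is met. Section 10.3.1 also allows a chi-square test. Without continuity correction, χ² = 50 × (5 × 25)² / (25 × 25 × 5 × 45) = 5.56, p = 0.018. The expected counts of 2.5 point to Fisher, but the outcome turns on that choice.

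Power of the two-sided Fisher test at 25 per arm (true rates assumed):

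| Control | Intervention | Power |
|---|---|---|
| 0% | 10% | 3% |
| 0% | 20% | 38% |
| 4% | 20% | 23% |
| 0% | 30% | 81% |
| 0% | 40% | 97% |

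**4. What an interval would say.** Newcombe 95% interval built from Wilson limits, z² = 3.84.

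- 0/25 against 0/25: the Wilson upper limit is 3.84 / (25 + 3.84) = 0.133, so the difference runs from −13.3 to +13.3 points.
- 5/25 against 0/25: the Wilson limits for 5/25 are 0.089 and 0.391. Lower limit 0.20 − √(0.111² + 0.133²) = 0.026; upper limit 0.20 + (0.391 − 0.20) = 0.391. The difference runs from about 3 to 39 points.

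The second result, which would meet the hypothesis in 10.1 under Fisher, is compatible with an excess of up to 39 points. The interval shows this and the significance reading hides it.

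**The case against.** The strongest reply is that the formal text already confines the verdict to CO2. The synopsis and 10.1 define non-inferiority on CO2 alone, and the local-language summary names CO2 wash-out as the main question. This stands. Neither the primary hypothesis nor the choice of a CO2 endpoint is at fault: the rationale treats apnoeic oxygenation as accepted and the ventilatory effect as the unproven part.

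A reader might infer that the local-language summary rests its oxygenation statements on the CO2 verdict. The documents do not support that. The summary never mentions non-inferiority. Its expectation is drawn from the study's findings in general, which can include the SpO2 outcomes, and its emergency sentence states a need. Section 3.4 is likewise a rationale. Only 2.1.1 makes the link, and in hedged terms.

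A reader might also infer that a large excess of desaturation would go unseen. That is not supported either: SpO2 is recorded, proportions are compared, and 0% against 40% would be detected with about 97% power. Small to moderate excesses remain the difficulty.

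Finally, it can be said that intervals for secondary outcomes belong in a statistical analysis plan, which is not at hand. That is fair for the method of calculation. It does not cover 10.1, which itself fixes a hypothesis of no significant excess, or the conditional sentence in 2.1.1.

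**Conclusion.** The concern holds in limited form. Section 2.1.1 attaches a safety benefit to a non-inferiority verdict that concerns CO2 clearance only and does not register early stops for SpO2 <92%. The one hypothesis in 10.1 that touches oxygenation does not close the gap: as worded it counts every reason for stopping, and an excess of 5 in 25 over 0 in 25 would meet it under Fisher's test.

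The primary test, its margin and the sample size are unaffected. What changes is what may be concluded about oxygenation. The Fisher and interval results are exact arithmetic for hypothetical counts. The true desaturation rates, the reading error, the stopping times and the two-sided 5% level are assumptions, since the protocol gives none of them.

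A reader might go further and require a pass/fail oxygenation margin before any lower flow is called usable. The documents set no such objective and 25 per arm could hardly serve it. With assumed completion rates of 98%, 95% and 90% in both arms, a 10-point margin at one-sided 0.025 and 80% power would need 31, 75 and 142 per group.

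**What to change.** 1. In 2.1.1 and the local-language summary, state that non-inferiority refers to CO2 clearance only and does not by itself support a claim about oxygenation or about avoiding desaturation.
2. In 10.1 and 10.3, replace the hypothesis of no significant excess with an estimate: for each intervention arm, the difference from control in the proportion reaching SpO2 <92% within 15 minutes, with a two-sided 95% interval, reported beside each CO2 verdict. List stops for the other criteria separately by arm.
3. Say in the same place that a non-significant comparison is not evidence of equal oxygenation.

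No oxygenation margin, extra patients or new measurements are needed. The cost is a few sentences and three intervals from data already collected. The drawback is that these intervals will be wide, about ±13 points even with no desaturation in either arm, so any statement that lower flows oxygenate as well becomes more cautious.

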### **Abbreviations**

|                 |                                                                                       |
|-----------------|---------------------------------------------------------------------------------------|
| AE              | Adverse Event                                                                         |
| BMI             | Body-mass index                                                                       |
| BP              | Blood pressure                                                                        |
| CA              | Competent Authority (e.g. Swissmedic)                                                 |
| CEC             | Competent Ethics Committee                                                            |
| CPAP            | Continuous positive airway pressure                                                   |
| CO 2 | Carbon Dioxide                                                                        |
| CRF             | Case Report Form                                                                      |
| EIT             | Electrical Impedance Tomography                                                       |
| GCP             | Good Clinical Practice                                                                |
| Ho              | Null hypothesis                                                                       |
| H1              | Alternative hypothesis                                                                |
| HFG             | Humanforschungsgesetz (Law on human research)                                         |
| HFNCT           | High Frequency Nasal Cannula Therapy                                                  |
| HMG             | Heilmittelgesetz                                                                      |
| HRA             | Federal Act on Research involving Human Beings                                        |
| IIT             | Investigator-initiated Trial                                                          |
| ITT             | Intention to treat                                                                    |
| KlinV           | Verordnung über klinische Versuche in der Humanforschung ( in English: ClinO ) |
| l/min           | Liters per minute                                                                     |
| MD              | Medical Device                                                                        |
| NIRS            | Near infra-red spectroscopy                                                           |
| p a  | Arterial partial pressure                                                             |
| p tc | Transcutaneous partial pressure                                                       |
| O 2  | Oxygen                                                                                |
| PI              | Principal Investigator                                                                |
| SDV             | Source Data Verification                                                              |
| SOP             | Standard Operating Procedure                                                          |
| THRIVE          | transnasal humidified rapid-insufflation ventilation exchange                         |
| TOF             | Train of four                                                                         |

